### Enzalutamide

Enzalutamide (Xtandi®, Astellas Pharma) has to be started together with the start of ADT.

### Premature discontinuation of trial treatment

Participants may voluntary withdraw their consent to participate in the Trial for any reason at any time. The participant’s request to withdraw from the Trial must always be respected without prejudice or effect on further treatment. Withdrawal of consent will be documented in the participant’s medical record. Trial data and samples collected before withdrawal can be used in the trial. No new trial data or samples will be collected after withdrawal of the participant. The investigator may also decide at any time during the course of the study to temporarily suspend or permanently discontinue the Trial treatment if continuation of the study would be detrimental to, or not in the best interest of the participant. Similarly, the Sponsor, Ethics Committee or authorized regulatory authority may decide to discontinue or prematurely terminate the Trial when new information becomes available whereby the rights, safety and well-being of Trial participants can no longer be assured, when the integrity of the Trial has been compromised, or when the scientific value of the Trial is outdated and/or unjustifiable. In any case of premature termination of the study and/or interruption/discontinuation of treatment, the Investigator will continue to monitor the participant’s condition and provide adequate medical care and follow-up. In all situations where study participation is discontinued, as well as when the study is completed as planned, the investigator will assess the participants health and prescribe the best treatment available at that time.

### Objectives

#### Primary endpoint

◦ Poly-Metastatic Free Survival (PMFS) will be determined from the last day of the first SBRT or from the day surgery was performed until the first day of poly-progression which is defined as the detection > 5 new lesions at PSMA PET-CT/MRI (± combined with MRI if needed to improve diagnostic accuracy). In case of poly-progression, pADT combined with chemotherapy [42–44], ARTA [28, 29, 31] or abiraterone-acetate [33, 34] will be considered the standard-of-care. The decision on which treatment will be offered will be taken on the multidisciplinary meeting in every case and will take into account former treatment. If recurrence occurs in ≤ 5 lesions, a new MDT is proposed if technically feasible and the patient will receive again the treatment he was allocated to at the time of initial randomisation. Patients free from poly-progression are censored at their last follow-up.

#### Secondary endpoints

◦ Metastatic Castration-Refractory Prostate Cancer Free Survival (mCRPC-FS) will be determined from the last day of the first SBRT or from the day surgery was performed until the first day of diagnosis of CRPC. CRPC is defined according to the contemporary EAU-guidelines as the time to biochemical and/or clinical progression at castrate testosterone levels (< 50 ng/dl). Biochemical progression is defined as three consecutive PSA rises (1 week interval), of which at least 2 rises with a PSA level of > 2 ng/ml and a rise of 50% above the nadir PSA level [45]. Patients free from CRPC are censored at their last follow-up.◦ Biochemical relapse-free survival (bRFS) will be determined from the last day of the first SBRT or from the day surgery was performed until the first day of BCR. BCR is defined as three consecutive PSA rises (1 week interval), of which at least 2 rises with a PSA level of > 2 ng/ml and a rise of 50% above the nadir PSA level. Patients free from BCR are censored at their last follow-up.◦ Clinical progression free survival (cPFS) will be determined from the last day of the first SBRT or from the day surgery was performed until the first day of clinical relapse. Patients free from clinical relapse are censored at their last follow-up. Clinical relapse is defined as the appearance of 1 new lesion with a high suspicion on PSMA PET-CT/MRI [46].◦ Cancer Specific Survival (CSS) will be determined from last day of the first SBRT or from the day surgery was performed until PCa death. Death of other causes is considered a competing event, while patients alive are censored at last follow-up.◦ Overall Survival (OS) will be determined from last day of the first SBRT or from the day metastasectomy was performed until death from any cause, with censoring of patients alive at last follow-up.◦ Acute and late toxicity score as a result of RT will be scores using the Common Toxicity Criteria Version 5.0 [47]. Toxicity will be scored at every visit during follow-up (see Table 1).◦ Quality of life scoring using the EORTC QLQ-C30 supplement with QLQ-PR25. We will assess the quality-of-life-years with the EuroQOL classification system (EQ-5D-5L). The questionnaires are administered at baseline, last day of treatment, and during follow-up consultation at month M1, M3, M6, M12 and M24 (see Table 1).

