### Inclusion criteria

All patients must fulfil the following inclusion criteria:• Histologically proven initial diagnosis of prostatic adenocarcinoma.• Prior treated and controlled primary tumor. Patients with local recurrence can be included only when accompanied by M1a-c disease, provided that the total number of active lesions does not exceed 5.• Biochemical recurrence defined by prostate-specific antigen (PSA) values > 0.2 ng/ml (i.e., two consecutive increases) following radical prostatectomy ± postoperative RT and a PSA value of 2 ng/ml above the nadir after high-dose RT and confirmed at least once [36].• Presence of oligorecurrent disease defined as a maximum of 5 extracranial metastases in any organ, diagnosed on PSMA PET-CT (PSMA PET-MRI is allowed, but optional) reported according to the E-PSMA consensus guidelines for interpretation of PSMA-PET [37]. Nodal (N1) disease can be included only when accompanied by M1a-c disease, provided that the total number of active lesions does not exceed 5.• Serum testosterone level within normal range.• WHO performance 0–2.• Age >  = 18 years old.• Willing to provide a signed informed consent.• Absence of psychological, sociological, or geographical condition potentially hampering compliance with study protocol.• Patients must be presented at the multidisciplinary board meeting and the inclusion in the trial needs approval by this board.

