### Interventions

All patients eligible for the trial will be recruited after a mandatory discussion on the multidisciplinary urology tumour board, and after approval from the attending physician if a patients is referred from another external treatment centre. Leuven University Hospitals has started recruitment in April 2022. Participating treatment centres will be added subsequently following the legal ethical requirements i.e. starting at least 3 months after inclusion of the first patient in Leuven University Hospitals. After being considered eligible, the patient will follow the trial procedure. At first, a screen visit is scheduled, on which the patient will receive a standard clinical examination and laboratory analysis including peripheral blood cell count with formula, liver and kidney function, alkaline phosphatase, lactate dehydrogenase, PSA and testosterone. Three Quality-of-life questionnaire (QLQ-30, QLQ-PR25 and EQ-5D) [38, 39] as well as a toxicity score will be carried out [40] after signature of the informed consent. Post-treatment follow-up will be planned according to the trial protocol: there are 5 follow-up visits (month 1 and further on 3-monthly basis) scheduled in year 1 and 3-monthly follow-up visits thereafter unless clinical evolution requires more monitoring. The timeline of the participants is shown in Fig. 2. The summary of the study visits is displayers in Table 1.

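### The bRFS event repeats the castration-resistance PSA rule, so relapse below 2 ng/ml in hormone-sensitive men can be missed or dated late

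*Protocol article*

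**What the plan says.** All references are to the protocol article.

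- **Secondary endpoints, bRFS.** The event is BCR: "BCR is defined as three consecutive PSA rises (1 week interval), of which at least 2 rises with a PSA level of" greater than 2 "ng/ml and a rise of 50% above the nadir PSA level. Patients free from BCR are censored at their last follow-up". No testosterone condition is attached.
- **Secondary endpoints, mCRPC-FS.** "CRPC is defined according to the contemporary EAU-guidelines as the time to biochemical and/or clinical progression at castrate testosterone levels" (below 50 ng/dl). The biochemical part reads: "Biochemical progression is defined as three consecutive PSA rises (1 week interval), of which at least 2 rises with a PSA level of" greater than 2 ng/ml, with the same 50% criterion.
- **Inclusion criteria.** "Biochemical recurrence defined by prostate-specific antigen (PSA) values" greater than "0.2 ng/ml (i.e., two consecutive increases) following radical prostatectomy", or 2 ng/ml above nadir after high-dose radiotherapy. Testosterone must be in the normal range; the exclusion criteria rule out castration levels.
- **Interventions and Table 1.** Blood samples are scheduled at the end of radiotherapy and at months 1, 3, 6 and 9, then quarterly. The text gives "3-monthly follow-up visits thereafter unless clinical evolution requires more monitoring".
- **Primary endpoint.** A recurrence in up to five lesions leads, where feasible, to new MDT together with the originally allocated treatment.
- **Secondary endpoints, cPFS.** One new highly suspicious PSMA PET lesion is an event, whatever the PSA.

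**The concern.** A rule introduced for progression under castration is reused to detect relapse in men who enter hormone-sensitive. Arm A receives no hormonal therapy, and arms B and C receive it for 1 and 6 months. The article gives no reason for the reuse.

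The 2 ng/ml floor is what matters. A man after prostatectomy may enter well below it, respond to MDT and then relapse with a clear, sustained PSA rise that never counts, or counts only much later. Meanwhile he can have a new lesion and be re-treated. On the wording of bRFS, re-treatment is neither an event nor a censoring time, so he stays at risk. Re-treatment brings hormonal therapy again in arms B and C but not in arm A. If that lowers PSA, as one would expect, it could postpone or prevent the recorded event in two arms only. The higher the floor, the longer the window in which this can happen.

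At stake is whether bRFS measures biochemical relapse after MDT, and whether its comparison between arms can be read cleanly.

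**Working it through.** The article states no figure for bRFS, so there is none to reproduce. The check compares the texts and then sizes the delay.

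**1. Text.** The bRFS rule and the biochemical part of the CRPC rule agree on the number of rises, the interval, the 2 ng/ml floor and the 50% criterion. The only difference is the missing testosterone condition.

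**2. Time between the two levels.** Inputs are 0.2 ng/ml (the lowest level at which the trial itself speaks of recurrence), 2 ng/ml (the bRFS floor) and a PSA doubling time DT. Only the 3-month DT comes from the article, as the stratification cut; the others are assumptions. Under exponential growth:

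delay = DT × log2(2 / 0.2) = 3.32 × DT

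| DT (months) | Delay (months) |
|---|---|
| 1 | 3.3 |
| 2 | 6.6 |
| 3 | 10.0 |
| 6 | 19.9 |
| 12 | 39.9 |

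**3. On the visit grid.** Assume a nadir at time 0, untreated exponential growth, samples every 3 months, and an event dated at the visit that completes the rule. The yardstick is two consecutive increases with PSA above 0.2 ng/ml. The bRFS rule is applied with the scheduled samples counted as its rises, ignoring the 1-week interval.

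| Assumed nadir (ng/ml) | DT 3: yardstick / bRFS | DT 6 | DT 12 |
|---|---|---|---|
| 0.02 | 12 / 24 | 21 / 45 | 42 / 84 |
| 0.1 | 6 / 18 | 9 / 30 | 15 / 57 |
| 0.5 | 6 / 12 | 6 / 18 | 6 / 30 |
| 1 | 6 / 9 | 6 / 12 | 6 / 18 |
| 1.9 or 3 | 6 / 9 | 6 / 9 | 6 / 9 |

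Entries are months. At nadir 0.1 and DT 3 the quarterly values are 0.1, 0.2, 0.4, 0.8, 1.6, 3.2 and 6.4. At month 12 the man has had four successive rises and a PSA 16 times his nadir, and has no event. The rule is met at month 18. With a nadir near or above 2 ng/ml, the lag is one visit.

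**4. Interval.** After month 1 the scheduled samples are 2 to 3 months apart, so no scheduled set supplies three rises one week apart.

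**The case against.** The strongest reply is that the entry rule and the bRFS rule serve different settings. The inclusion criterion describes recurrence after primary treatment. bRFS concerns relapse after MDT in men already known to have metastases. Two thresholds for two settings are not in themselves a contradiction, and nowhere does the article say that the entry rule governs follow-up. This stands: 0.2 ng/ml is used above only as a yardstick.

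It also means that the entry thresholds should not be copied into bRFS. A man whose PSA stays above 0.2 after MDT would relapse at any confirmed rise. For two men with a nadir of 0.1, the event would come at 0.2 after prostatectomy and at 2.1 after radiotherapy. That gap of log2(10.5) = 3.4 doublings, about 10 months at DT 3, does not exist under the present uniform rule. A very low threshold might also pick up PSA rises that accompany testosterone recovery in arms B and C; the article is silent on this.

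A reader might infer three stronger things that the article does not support:

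- **That the intended order of endpoints is reversed.** No order or hierarchy of secondary endpoints is stated, and an imaging relapse that comes first is captured by cPFS.
- **That the rule biases results by prior primary treatment, which is not a stratification factor.** The rule is the same for everyone. The difference appears only against the entry thresholds, and leaving a factor out of the stratification does not bias a randomised comparison.
- **That weekly rises can never be observed.** The Interventions section allows extra monitoring when clinical evolution requires it. What remains is a mismatch with the scheduled samples, and an ambiguity that sites may resolve differently.

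None of this explains why a castration-resistance rule, stripped of its castration condition, should define relapse in these men.

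**Conclusion.** The concern holds in this form: as written, bRFS can miss or date late a sustained PSA relapse below 2 ng/ml, and its interval does not match the visit schedule.

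The size is conditional. For a low post-MDT nadir (0.02 to 0.1 ng/ml), the lag on quarterly visits is about 12 months at a doubling time of 3 months, 21 to 24 months at 6 and 42 months at 12. It falls to one visit at nadirs near or above 2 ng/ml. These figures assume untreated exponential growth. The article gives no distribution of entry PSA, post-MDT nadir or doubling time, and no share of men after prostatectomy, so the average effect on the trial cannot be computed.

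That some relapses are never recorded is a plausible scenario, through re-treatment or end of follow-up below the floor, but it has no number behind it. The same holds for a difference between arms caused by repeated hormonal therapy.

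bRFS is one of several secondary endpoints. PMFS, the sample size and the interim rules do not use it. The wording should be changed, but the trial's main conclusion does not depend on it.

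**What to change.** 1. Give bRFS its own event definition, separate from the CRPC rule: a confirmed PSA rise above the post-MDT nadir, able to register relapse below 2 ng/ml and applied identically in all arms. Fix and justify the size of the rise in advance. Do not carry over the entry thresholds unchanged.
2. State how the analysis treats PSA rises during testosterone recovery in arms B and C.
3. State how the analysis treats re-treatment before any PSA event (as an event, as censoring or ignored), and the reason.
4. Replace the 1-week interval by *at least 1 week apart*, so that scheduled values can be used.
5. Keep the 2 ng/ml and 50% rule for CRPC, and report bRFS under the present rule as a sensitivity analysis.

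The cost is endpoint wording plus one extra analysis, using PSA values from samples already scheduled. If item 2 is to rely on testosterone values, confirm that the follow-up samples include them; the article names testosterone only at screening. The change should be made before outcomes are examined by arm.

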**Methods & design:**

Patients diagnosed with oligorecurrent HSPC (defined as a maximum of 5 extracranial metastases on PSMA PET-CT) will be randomized in a 1:1:1 allocation ratio between arm A: MDT alone, arm B: MDT with 1 month ADT, or arm C: MDT with 6 months ADT together with ARTA (enzalutamide 4 × 40 mg daily) for 6 months. Patients will be stratified by PSA doubling time (≤ 3 vs. > 3 months), number of metastases (1 vs. > 1) and initial localization of metastases (M1a vs. M1b and/or M1c). The primary endpoint is PMFS, and the secondary endpoints include mCRPC-FS, biochemical relapse-free survival (bRFS), clinical progression free survival (cPFS), cancer specific survival (CSS), overall survival (OS), quality of life (QOL) and toxicity.

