## Methods/design

### Study design

SPARKLE (a new **S**park in treating oligorecurrent **P**rostate cancer: **A**dding systemic treatment to stereotactic body **R**adiotherapy or metastasectomy: **K**ey to **L**ong-lasting **E**vent-free survival?) is approved by the Ethics committee of the Leuven University Hospitals (LUH) (EC2022/S65935) and is registered at the EudraCT data base (2022–000,066-18) and at clinicaltrials.gov (NCT05352178). It is a prospective, multicenter, randomized, open-label, three-arm, phase III study. The aim is to investigate whether the addition of short-term ADT during 1 month or short-term ADT during 6 months together with an ARTA to MDT significantly prologs polymetastatic-free survival (PMFS). The following arms will be compared (1:1:1) (Fig. 1):1. Arm A: MDT alone2. Arm B: MDT + 1 month of ADT3. Arm C: MDT + 6 months of ADT together with 6 months ARTA (enzalutamide)

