#### Data analysis

Patients will be analysed in the groups to which they are assigned (intention-to-treat). A stratified two-sided log-rank test will be used for the three pairwise comparisons of the primary analysis, to test for a difference between the three treatment arms with regards to poly-metastasis free survival (PMFS). A Bonferroni correction will be applied to guarantee a study-wise 5% significance level for the primary endpoint. Stratification factors are PSA doubling time (≤ 3 vs. > 3 months), number of metastases (1 versus > 1) and initial localization of metastases (M1a vs. M1b and/or M1c). Kaplan–Meier estimates will be obtained, and a KM curve will be constructed. The hazard ratio (HR) will be determined with 95% confidence interval by means of a Cox proportional hazards model. For the evaluation of mCRPC-FS, cPFS and OS the same method will be used as for the primary endpoint. CSS will be estimated using the cumulative incidence function rather than the Kaplan–Meier estimates to count for death of other causes as a competing event.

Group differences with regards to longitudinally measured ordinal outcomes such as toxicity will be analysed by means of proportional odds models with estimation based on generalized estimating equations (GEE). Multiple imputation will be applied in case of considerable drop-out, providing consistent estimates under a missing-at-random (MAR) drop-out pattern, hence when the probability of drop-out depends on treatment group or previous observations. Group differences with regards to longitudinally measured continuous outcomes such as quality of life scores will be analysed by means of linear mixed models. Likelihood methods will then be used for parameter estimation providing valid inference under MAR. For all longitudinal analyses, the explanatory model will contain both treatment group, time point of measurement and their interaction in order to test post-hoc group effects at specific time points. Statistical analysis will be performed using SAS software.

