### Monitoring

All research physicians and research centres meet the qualification requirements of the responsible Ethics Committee in terms of professional training, experience in clinical trials and equipment. Because the trial medication is well characterized and of a low risk, no Data Monitoring Committee has been set up. Investigators will seek information on the occurrence of safety events at each participant contact. All events, whether reported by the participant or noted by Trial staff, will be recorded in a timely manner in the participant’s medical record and in the eCRF. The following minimum information will be recorded for each event: event description, start and stop date of the event, severity, seriousness, causality assessment to the IMP and/or Trial procedures, outcome. The Investigator will grant direct access to research data and documents for the purpose of monitoring, audits and/or inspections by authorized entities. As such eCRFs, source records and other study-related documentation (e.g. Investigator Site File, the Trial Master File, pharmacy records, etc.) will be kept current, complete and accurate at all times. All protocol modifications will be registered in the clinical trial protocol history. Protocol amendments will be submitted in writing to the responsible Ethics Committee and the national competent authority. All serious adverse events (SAEs) must be reported by reported within 24 h of the Investigator’s first awareness of the information. This is also the case for previously non-serious AEs which subsequently become SAEs. If the Investigator or research team becomes aware of an SAE with suspected causal relationship to the IMP or experiment, after the participant has completed the Trial, this SAE must be reported within the same timelines as for SAEs occurring during the Trial.

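### The toxicity endpoint is defined as radiotherapy-attributed only, which fits neither the randomised contrast nor the unrestricted use of toxicity elsewhere in the protocol

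*Protocol article*

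**What the plan says.** In the protocol article, Secondary endpoints defines toxicity by its cause: "Acute and late toxicity score as a result of RT will be scores using the Common Toxicity Criteria Version 5.0". The sentence that follows sets the schedule and does not repeat the restriction: "Toxicity will be scored at every visit during follow-up (see Table 1". No other section defines a toxicity endpoint for ADT, enzalutamide or surgery.

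The randomised question is about systemic therapy. Study design states it so: "The aim is to investigate whether the addition of short-term ADT during 1 month or short-term ADT during 6 months together with an ARTA" prolongs polymetastatic-free survival when added to MDT. MDT may be SBRT or metastasectomy, and the time origin of the time-to-event endpoints allows for both: "from the last day of the first SBRT or from the day surgery was performed".

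Elsewhere toxicity is unqualified. The abstract lists "overall survival (OS), quality of life (QOL) and toxicity" among the secondary endpoints. Data analysis plans a formal comparison: "Group differences with regards to longitudinally measured ordinal outcomes such as toxicity will be analysed by means of proportional odds models", estimated by GEE with group, time point and their interaction. Interventions asks for a toxicity score at screening. Monitoring requires that "All events, whether reported by the participant or noted by Trial staff, will be recorded in a timely manner", with severity and "causality assessment to the IMP and/or Trial procedures" among the items noted for each event.

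**The concern.** A between-arm comparison of harm should be able to register harm from whatever differs between the arms. Here the first MDT is common to all arms and the drugs are what is randomised. An endpoint that counts only events judged to be caused by radiotherapy is aimed at the shared component.

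The trial has to weigh a delay in polymetastatic disease against the burden of added hormonal treatment. That treatment can be given more than once, because Primary endpoint has the patient receive his allocated treatment again at a recurrence of 5 lesions or fewer. If the toxicity model is fed only radiotherapy-attributed grades, it could show little difference between arms A and C while arm C carries more drug-related toxicity. A reader of the results could then take a finding on the toxicity endpoint as a statement about the tolerability of the regimens, which it would not be.

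**Working it through.** There is no figure to reproduce: the point depends on no significance level, power, effect size or event count. The check is to set the sections side by side.

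| Place in the protocol article | What it covers | Limited to radiotherapy? |
|---|---|---|
| Secondary endpoints, toxicity, definition | acute and late toxicity, CTC version 5.0 | yes |
| Secondary endpoints, toxicity, schedule | scoring at every follow-up visit | not stated |
| Abstract, Methods & design | toxicity as a secondary endpoint | no |
| Interventions | toxicity score at screening | not stated; precedes trial radiotherapy |
| Data analysis | proportional odds/GEE comparison of arms | no |
| Monitoring | all events, with severity and causality | no |

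**Step 1: definition against the randomised contrast.** Arms A, B and C receive 0, 1 and 6 months of ADT, with enzalutamide for 6 months in arm C only. Toxicity attributed to these drugs is outside the definition.

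**Step 2: definition against the population.** The analysis is by intention to treat, so patients whose MDT is metastasectomy are included. Until such a patient receives trial SBRT, he has no trial radiotherapy to which toxicity could be attributed. His surgical and hormonal toxicity falls outside the endpoint.

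**Step 3: definition against the analysis.** Data analysis names toxicity as the outcome without restating what it is. The only definition available to whoever implements the model is the radiotherapy-attributed one. Followed as written, the outcome is a grade that has first passed an attribution decision. The trial is open-label, so that decision is made with the arm known.

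**Step 4: what else compares the burden of treatment between arms.** Quality of life does, at baseline, the last day of treatment and months 1, 3, 6, 12 and 24. The sample-size section assumes a median polymetastatic-free survival of 21 months in arm A, hence 21 + 12 = 33 months in arm B and 33 + 12 = 45 months in arm C, and a minimum of 5 years (60 months) of follow-up. Repeat treatment courses can therefore fall after the last questionnaire. Toxicity is scored at every visit, so it is the tolerability endpoint that continues past month 24.

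**Step 5: what is collected in any case.** Monitoring captures all events with a causality assessment. The data for a broader endpoint therefore largely exist. One gap remains: that section asks for severity and does not name CTCAE grading.

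**The case against.** The strongest reply is that the protocol does not ignore drug harm. A reader might infer from the endpoint definition that it does, and the document does not support that. Monitoring has events sought at every contact and recorded whatever their cause, with causality to the investigational product, and serious events reported within 24 hours. This stands: the harms are collected. What is in doubt is whether they enter the defined endpoint and its comparison.

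Second, the restriction appears in one sentence only, and the abstract, the analysis section and the screening score do not share it. This also stands. The protocol is inconsistent; it does not show a settled decision to exclude hormonal toxicity. The screening score is weak evidence by itself, because a baseline is useful for a radiotherapy score too.

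Third, a reader might infer that radiotherapy-attributed toxicity must be almost the same in arms A and C. That does not follow. A recurrence of 5 lesions or fewer leads to a new MDT where feasible, so if systemic therapy delays recurrence, cumulative radiotherapy exposure would differ by arm. The team's own retrospective series had 314 MDTs in 191 patients (314/191 = 1.64 per patient), with 13% receiving three or more. Radiotherapy toxicity by arm is therefore a legitimate question, and a reason to keep it as a subset.

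Fourth, it is tempting to say that surgical patients cannot score at all. They can, if a later recurrence is treated with SBRT. The definition fits them poorly; it does not shut them out for good.

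Finally, adverse-event tables by arm may be in the full protocol or analysis plan. Their absence from the article is no fault and is not part of this point. An endpoint definition that is stated too narrowly is a different matter, because an analysis plan would normally take it over.

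**Conclusion.** The point holds as a mismatch of definition. The stated toxicity endpoint is narrower than the endpoint named in the abstract, the outcome named in the analysis and the events recorded under Monitoring, and it does not address what the arms differ in. Taken literally, the proportional odds comparison would exclude toxicity attributed to ADT, enzalutamide or surgery.

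The size is qualitative. The article gives no toxicity rates, so the difference that would be missed cannot be calculated. The primary endpoint and sample size are unaffected. The conclusion rests on two assumptions: that the definition under Secondary endpoints governs the outcome used in the model, and that the documents not shown do not replace it. If the unrestricted reading was intended, the correction is one of wording only. It should be made either way, because this endpoint carries much of the harm side of the trial's question.

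**What to change.** Redefine the endpoint under Secondary endpoints as acute and late toxicity of any cause, graded by CTCAE v5.0 at every visit in all patients whatever their MDT, for example as the worst grade per visit. State that this is the outcome compared by arm in the proportional odds/GEE analysis. Report radiotherapy-attributed toxicity as a subset, so that the effect of repeat MDT stays visible.

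Toxicity of all trial treatments would be an alternative. It would cover the drugs and surgery but keep an open-label attribution step. An any-cause grade removes that step, though not the subjectivity of open-label grading.

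The cost is small: one reworded definition, one more table, and a statement in Monitoring that recorded events are graded by CTCAE v5.0, since it now says only severity. In the same edit, Table 1 could name toxicity scoring: the endpoint text refers to that table for it, but the table lists only follow-up, blood sampling and questionnaires. An any-cause grade also counts unrelated background events, which may dilute a difference; the attributed subset helps the reader to see this.
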